#### Demographic and medical/treatment-related data

Demographic, medical and treatment related data include information on age, living arrangements, marital and work status, level of education, body mass index, cancer stage, tumour characteristics, type of surgery and adjuvant treatment regimen including radiotherapy.

#### Self-reported data

*Distress* will be used as the primary outcome and is assessed using the Distress Thermometer [28]. The instrument consists of an 11-point numeric scale ranging from 0 to 10 (0 = no distress; 10 = extreme distress) and a problem list comprising 35 common problems in cancer patients, divided into five categories: practical problems, family-related problems, emotional problems, spiritual or religious problems, and physical problems, answered with “Yes” or “No”. The Distress Thermometer has been shown to be valid [11, 35] and have good potential as a screening tool for distress-related practical, family, emotional and physical problems in patients with cancer in a Swedish population [28, 35].

*Quality of life* will be evaluated using European Organization for Research and Treatment of Cancer (EORTC)-validated instruments including the general QoL instrument, QLQ-C30 v3.0 [36], and its BC-specific module, QLQ-BR23 [37]. The instruments consist of symptom and functional scales and are answered on 4 and 7-point Likert scales.

*Anxiety and depression* will be evaluated using the Hospital Anxiety and Depression Scale (HADS) [38] containing 14 questions answered on a 4-point Likert scale (0–3). The scale has shown sound psychometric properties in women with BC [39].

*Resilience* will be evaluated using the Connor-Davidson Resilience Scale (CD-RISC) [40] incorporating 25 items answered on a 5-point Likert scale (0–4). The scale has good psychometric properties [41] and is shown to be valid and reliable in a Swedish population [42].

*Physical activity and health-related behaviours* will be evaluated using single items collected from validated instruments from the Swedish National Board of Health and Welfare. Items related to physical activity will include questions about exercise and activity, while items related to health behaviours will include questions on tobacco and alcohol consumption, and nutrition.

*Care satisfaction* will be evaluated using single items inspired by a evaluation form related to care process, support and the comprehensiveness of the system developed by the Regional Cancer Centre (RCC), Sweden.

#### National register data

Health economic evaluations will be conducted based on register data and focus on health care utilization and sickness absence. Data regarding health care utilization within public inpatient and outpatient care will be collected from the National Patient Register, and data regarding sickness absence from the Swedish Social Insurance Agency.

#### Focus group interviews

Focus group interviews aiming to illuminate patients’ and their relatives’ experiences of the rehabilitation process after participation in the RCT study will be conducted to provide a deeper understanding of the effect of the RCT. Aiming for maximum variation related to age, type of treatment and group (IG or CG), a purposeful sample of patients and relatives will be invited to participate. Three focus group interviews per participant category (patients from the IG, and the CG, and their relatives) will be conducted using a semi-structured interview guide. The interviews will be audio-recorded and transcribed verbatim. Data will be analysed using conventional qualitative content analysis [34].

#### Data management and monitoring

An electronic case report form (eCRF) is used for registration of demographic and medical/treatment-related data. All data are to be completed in the eCRF within 2 months of the follow-up contacts. Self-reported instrument data are collected and stored in a system for instrument data. Data monitoring is performed inspired by the Good Clinical Practice (GCP) guidelines. In the pilot study (*n* = 90) and with the first 30 patients included in the full-scale study, completeness of data was monitored for all patients to ensure that potential systematic errors would be identified. Monitoring for all subsequent patients will be conducted twice a year. Data on items identified as specifically important, e.g. Distress Thermometer score, informed consent and randomization, will be monitored for all patients, while all other included data will be monitored for every 10th patient. Data monitoring will be performed by an independent monitor. No data monitoring committee (DMC) will included due to the characteristics of the study and local standards. The eCRF data, instrument data and register data will be merged when data collection is closed. Only the research group members will have access to the full trial dataset.

#### Analytical plan

Statistical analyses based on data level and data distribution will be conducted using the IBM SPSS Statistics for Windows, Version 21.0 (IBM Corp, Armonk, NY, USA). An intention-to-treat analysis will be adopted to manage missing data and imputation of missing values will be conducted according to the instructions for each instrument. For health economic evaluations, the number of full-time equivalents (whole days of sick leave/patient) will be calculated in the first year after cancer diagnosis. Furthermore, the mean time from diagnosis to return to full-time work will be analysed, as a complement to full-time equivalents to illustrate a possible change in the dynamics of rehabilitation. An evaluation of the Distress Thermometer as an indicator for extended rehabilitation needs in the Swedish context will be conducted with the aim to establish the optimal cut-off for distress. Data from the Distress Thermometer and HADS will be used. A receiver-operating characteristic (ROC) analysis of distress, with HADS as the golden standard, will be conducted evaluating sensitivity, specificity and positive/negative predictive value.

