#### Sample size

Approximately 40% of the included patients are expected to suffer from increased distress (scoring ≥5 on the 0–10-point Distress Thermometer) and therefore to be available for randomization. A power calculation with distress as the primary outcome indicated that, with an expected reduction in distress of 1.0, a standard deviation (SD) of 2.9 and the significance level set at 0.05, approximately 300 patients are needed to achieve 80% power. When considering the proportion of patients scoring ≤4 on the Distress Thermometer and adjusting for expected dropout, a total of 950 patients will need to be included to ensure relevant power. Inclusion was started in May 2019 and will be running for approximately 5 years with an expected recruitment rate of 200 patients annually.

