#### Intervention group (IG)

Patients randomized to the IG will, in addition to “care as usual”, be offered an individualized rehabilitation plan based on the decision support tool developed in phase I. The decision support tool is structured with focus on patients’ health-related behaviours (e.g. nutrition, tobacco and alcohol consumption, and exercise) and on clinically and evidence-based knowledge about known problem areas for patients with BC. These areas are practical/relational problems (e.g. family or work-related problems), physical problems (e.g. fatigue or pain) and psychological/emotional and existential problems (e.g. worry, anxiety, and spiritual or religious problems).

The decision support tool will be used as a support in the dialogue between the patient and a dedicated research nurse and is structured in four steps. In the *first step* all patients will receive general advice about rehabilitation and exercise. The *second step* will focus on identifying patients’ individual needs, which in the *third step* will be matched to evidence-based interventions. In the *fourth step* the patient and the research nurse will decide on a rehabilitation plan with explicit goals for the rehabilitation process. They will also decide how the most effective follow-up can be organized. The rehabilitation plan will be evaluated based on the patients’ individual needs but as a minimum at 2 weeks after start of treatment and once a month during the first 3 months. The research nurse will act as a continuous health care contact and will be responsible for proactively and systematically evaluating the patient’s needs to ensure that potential new problems or changed rehabilitation needs are identified throughout the 1-year follow-up period and to promote retention and completeness of follow-up. An example of how the decision support tool works within the problem area of “fatigue” is given in Fig. 4.

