#### Data collection

Four data sources are used for data collection. Demographic and medical/treatment-related data are retrieved from the patients’ medical record. Self-reported data are collected using validated instruments at inclusion (1–2 weeks after cancer diagnosis, filled in at the outpatient centre) and 2 weeks and 3, 6, 9- and 12-months post start of treatment. Instruments are sent to patients by mail together with a pre-stamped envelope; and two reminders will be sent. Data collection are also conducted through national register data and through interviews with patients and relatives.

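### The stated missing-data rule leaves a missing primary outcome untreated: intention-to-treat supplies no values, and item-level imputation would not be expected to fill a single 0–10 score

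*Protocol article*

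**What the plan says.** All places are in the protocol article.

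- **Analytical plan**: "An intention-to-treat analysis will be adopted to manage missing data and imputation of missing values will be conducted according to the instructions" for each instrument. No other treatment of missing outcomes is stated, and no model for the primary comparison is named.
- **Self-reported data**: distress "will be used as the primary outcome and is assessed using the Distress Thermometer". On the form of the score: "The instrument consists of an 11-point numeric scale ranging from 0 to 10". The 35 Yes/No problems that accompany it are a separate list. By contrast, the HADS has 14 items and the CD-RISC 25.
- **Data collection**: after inclusion, scores are due at "2 weeks and 3, 6, 9- and 12-months post start of treatment". On procedure: "Instruments are sent to patients by mail together with a pre-stamped envelope; and two reminders will be sent". Neither the mailing nor the reminders are limited to one arm.
- **Intervention group (IG)**: the research nurse's continuing contact over the year serves, among other purposes, "to promote retention and completeness of follow-up". The section on the control and observational groups gives those women usual care and describes nothing comparable.
- **Sample size**: about 300 randomised women are needed, about 40% of those included are expected to qualify, and after "adjusting for expected dropout, a total of 950 patients will need to be included". The dropout rate is not given.

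**The concern.** The sentence in the Analytical plan assigns two tools to missing data, and neither fits the primary outcome.

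Intention-to-treat is a rule about the analysis set: every randomised woman is counted in the arm she was allocated to. It does not say what value stands in for a score that was never recorded.

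An instrument's imputation instructions normally estimate an unanswered item from the answered items of the same scale. That can work for the QLQ-C30, HADS or CD-RISC. A single rating has no companion items, and a questionnaire that never comes back has no answered items at all.

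What is at stake is the randomised comparison of the primary outcome. If loss is related to distress and differs between arms, an analysis that ignores it is biased. The trial collects five post-baseline scores per woman that could limit this, and the stated rule does not call on them.

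**Working it through.** **1. The plan's own figure for loss.** Inputs from the Sample size section: about 300 randomised women needed, 40% eligible for randomisation, 950 included.

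- Included before allowing for dropout: 300 / 0.40 = 750.
- Implied dropout: 1 − 750/950 = 0.21.
- The same in randomised women: 950 × 0.40 = 380; 380 − 300 = 80; 80/380 = 21%.

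The total of 950 is therefore consistent with about 300 needed and about 21% loss. (The figure of about 300 is not itself reproduced. With a difference of 1.0, SD 2.9, two-sided 0.05 and 80% power, 2 × (1.960 + 0.842)² × 2.9² / 1.0² is about 132, rounded up to 133 per arm or 266 in all. This is a separate matter on the conservative side, and nothing below depends on it.)

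**2. What the rule does with those 80 or so women.**

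| Situation | Intention-to-treat | Instrument instructions |
|---|---|---|
| One item blank in a multi-item scale | keeps the woman in her arm | can fill the item from the others |
| Distress rating blank | keeps her in her arm, supplies no score | no companion items to use |
| Questionnaire not returned | keeps her in her arm, supplies no score | nothing answered to use |

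The last two rows are the ones that matter for the primary outcome. The rule gives no value and no method for either.

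**3. Size of a possible bias (illustration; every input in this step other than the 1.0-point effect, the SD of 2.9 and the 380 randomised is assumed).** Let d be the share missing in an arm and g the mean distress of non-responders minus that of responders in the same arm. The responders' mean then lies d × g below the full-arm mean. If g is the same in both arms, the contrast among responders (control minus intervention) equals the true contrast minus (d_CG − d_IG) × g.

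- 15% missing in IG and 27% in CG (average 21%), g = 1: 0.12 × 1 = 0.12.
- Same split, g = 2: 0.12 × 2 = 0.24.
- 21% in both arms, same g: 0 × g = 0.

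A true benefit of 1.0 would appear as 0.88 to 0.76. If IG rather than CG lost more women, the sign would reverse and the benefit would be overstated.

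**4. What that means for power.** With 190 randomised per arm and SD 2.9:

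- Equal 21% loss: 150 per arm, SE = 2.9 × √(2/150) = 0.335; 1.0/0.335 − 1.96 = 1.03; power 0.85.
- 15%/27%: 161.5 and 138.7 women, SE = 2.9 × √(1/161.5 + 1/138.7) = 0.336. For 0.88: 0.88/0.336 − 1.96 = 0.66, power about 0.75. For 0.76: 0.76/0.336 − 1.96 = 0.30, power about 0.62.

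**The case against.** The strongest reply is that this is a condensed article. A statistical analysis plan may exist, and the choice of model and of sensitivity analyses is commonly left to it. That is right as far as it goes, and the absence of a named model is not the point here. The article does state a missing-data method, and the stated method misassigns the role of intention-to-treat. The published sentence would need correcting even if a sound analysis plan stands behind it.

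Several stronger readings are tempting, and the documents do not support them:

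- *Retention is promoted in the intervention arm only.* The mailed questionnaires and two reminders are not restricted to an arm, and the section on data management and monitoring has the Distress Thermometer score checked for all patients. What is supported is an additional effort in the intervention group.
- *The nurse chases questionnaires, and that task should be taken from her.* No section says so. Her contact through the year is part of the intervention, and the reminder procedure already reads as common to all groups.
- *The primary analysis will be a complete-case analysis.* No model is named, so this is an inference. A repeated-measures analysis is not excluded.
- *The rule cannot work at all.* The instrument's instructions are not shown. The conclusion rests on the single-item structure of the score.
- *The plan expects 30% loss.* That figure comes from setting 266 against 380 and borrows the separate sample-size discrepancy. The plan's own chain gives about 21%.
- *Missingness will differ by arm.* The documents give no dropout by arm. They describe a mechanism by which it could.

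**Conclusion.** The point holds in this form: the Analytical plan presents intention-to-treat as a way of handling missing data and otherwise relies on instrument instructions that would not be expected to apply to a one-item score. Missing primary-outcome scores are therefore left untreated by the stated rule, in a trial whose sample size implies about 21% loss, or about 80 of 380 randomised women.

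The extra retention effort in the intervention group makes arm-dependent loss possible, not established. The bias of 0.12–0.24 points rests on assumed missingness of 15% and 27% and an assumed excess of 1–2 points among non-responders. In that scenario it pulls the estimate towards no effect. It is zero if loss and excess are equal in the two arms, and its direction is not known from the documents.

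**What to change.** Replace the sentence in the Analytical plan with separate statements:

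1. **Analysis set.** Intention-to-treat means that all randomised women are analysed in their allocated arm.
2. **Primary outcome.** A likelihood-based repeated-measures model uses every available Distress Thermometer score at 2 weeks and 3, 6, 9 and 12 months, with baseline score, arm, visit and arm-by-visit. State that it is valid under missing at random, and read the primary contrast at the visit designated as primary. The baseline score should be available for every randomised woman, because it decides randomisation.
3. **Sensitivity analysis.** A delta-adjusted analysis, with shifts allowed to differ by arm, covers data missing not at random. The model in item 2 does not remove bias when loss depends on the unseen score, so this step is needed.
4. **Multi-item scales.** Keep the instrument imputation rules for these only.
5. **Reporting.** Give missingness of the primary score by arm and visit.

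The cost is a change of wording and a little extra analysis work. No new data, patients or contacts are required, and the nurse's role is unchanged. The wording should be settled before the data sources are merged at the close of data collection.

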## Discussion

The initial phases of this complex intervention study have created a solid base for the RCT, which has been pilot- and feasibility tested. This project has the potential to explore effective approaches to early identification and intervention in patients treated for BC with risk of developing poor outcome and unmet needs, which may have a beneficial impact for the patients as well as on health care resources. Despite extended research in the field of BC rehabilitation there is still a gap of knowledge regarding rehabilitation from a comprehensive perspective. This means that extended knowledge about how to identify patients with extended needs, and how individualized rehabilitation interventions can be practised, is fundamental for further development of BC rehabilitation. The ReScreen study builds on available knowledge about the effectiveness of specific interventions and will contribute to greater knowledge about the effectiveness of screening-based, individualized rehabilitation from a patient, relative and health economic perspective.

To our knowledge, there are no standardized methods for screening and meeting each individual’s rehabilitation needs after primary BC diagnosis. However, it has been suggested that by using a holistic, long-term approach integrating multi-professional and multi-disciplinary teams, cost-effective, patient-centred rehabilitative care can be achieved [43]. The present study has the potential to investigate several factors that may affect BC patients’ access to rehabilitation and identify important factors in implementing individualized rehabilitation.

Two studies have previously evaluated the Distress Thermometer as a screening tool to identifying patients suffering from moderate to severe distress [18, 24]. According to Ploos et al. [18] early screening has the potential to identify patients at highest risk of being chronically distressed, indicating that high distress could be used as an indicator for extended rehabilitation needs. The present study will contribute to knowledge of how to identify women experiencing high distress after BC diagnosis as an indicator of extended rehabilitation needs. By exploring the association between distress and self-reported or medical related data, the factors that explain the cause of high distress can be identified. Minimizing the negative effects of these factors will result in optimized rehabilitation.

Health economic aspects such as health care utilization and sickness absence are important when evaluating the effect of intervention studies. However, these aspects are sparsely evaluated when testing the effect of rehabilitation interventions. This means that an important piece of knowledge is missing when laying the ground for health care development and implementation. To our knowledge, this study is the first that will provide health economic evaluations of the effect of early identification of rehabilitation needs and individualized rehabilitation focusing on health care utilization and sickness absence – information that is important for future development towards individualized rehabilitation within the BC area.

This study focuses on developing and evaluating a clinically relevant model that is feasible in today’s complex health care system. Through these efforts, we provide an intervention that, if shown to be effective, can be implemented in clinical practice. This means that this project could benefit patients at an early stage after study evaluation and may in the near future change clinical practice.

## Data Availability

Not applicable.

## Abbreviations

BC: Breast cancer
CD-RISC: Connor-Davidson resilience scale
CG: Control group
eCRF: Electronic case report form
EORTC: European Organisation for Research and Treatment of Cancer
GCP: Good clinical practice
HADS: Hospital anxiety and depression scale
HCP: Health care professional
IG: Intervention group
OG: Observational group
QoL: Quality of life
RCC: Regional Cancer Centre
RCT: Randomized controlled trial
ROC: Receiver-operating characteristic
SD: Standard deviation
